**Fig. 4 Fig4:**
[figure not shown]
Pictorial presentation of the gait test: participants are asked to walk, cross an obstacle, and perform a visual search task presenting in the monitor while walking. Data from three consecutive gait cycles (i.e., two footsteps per cycle) are collected and analyzed, including one cycle before obstacle crossing, one cycle while crossing the obstacle (or stepping onto a marked position for the no-obstacle condition), and another cycle after crossing the obstacle. To accommodate participants with different walking speed, the visual stimuli will be presented after he/she walks pass the infrared sensor which is located at 1.5 m before the obstacle

Participants’ gait performance is recorded using the Vicon Motion System (Vicon Nexus 2.11, Oxford, UK). Twenty-seven reflective markers are placed on the head, trunk, and lower body according to the Vicon Plug-in full body gait model. All participants are asked to walk barefoot along a 6.2-m walkway at their normal comfortable towards a monitor at the end of the walkway, which presents a visual search task. Two impediments are introduced during the walk: physical obstacles and a visual search task. The obstacles can be gray for low contrast or yellow for high contrast, and either 5 or 15 cm in height. The base of the obstacle is 2.5 × 60 cm and positioned in the middle of the pathway. Participants’ gait parameters are measured under these conditions: (1) with or without an obstacle (5 sub-conditions: no obstacle; 5 cm gray obstacle; 5 cm yellow obstacle; 15 cm gray obstacle; 15 cm yellow obstacle) and (2) with or without a visual task (2 sub-conditions: fixation vs. Chinese character search). Five repetitions for each condition are recorded. Data from three consecutive gait cycles are collected and analyzed, including one cycle before obstacle crossing, one cycle while crossing the obstacle (or stepping onto a marked position for the no obstacle condition), and another cycle after crossing the obstacle (1 preparation, 1 obstacle crossing, 1 visual search). Gait parameters of the dominant leg are measured at 4 time points (T1, T4, T5, and T6) for each of the three cycles. These parameters include hip flexion/extension (the minimum/maximum angle in degrees), knee flexion/extension (the minimum/maximum angle in degrees), ankle flexion/extension (the minimum/maximum angle in degrees), head down/up (the minimum/maximum angle in degrees), walking speed (mm/s), stride length (mm), swing phase (%), and visual task accuracy (Appendix 1).

Balance testThe Bertec Balance Advantage™ system (Bertec Corporation, Columbus, OH, USA) is used to assess participants’ balance before and after training. During the test, participants are asked to stand under different challenging conditions. Balance-challenging conditions include (1) standing on a firm or foam surface (Fi/Fo); (2) standing surface with backward or forward translation (BT/FT); and (3) standing with their eyes close (EC). Cognitively-challenging conditions include a visual search task (fixation vs. Chinese character search; see below). Standing surface and translation conditions are combined with a randomly presented visual task and allocated to participants. Besides, additional EC conditions are set for participants when they stand on the firm and foam surfaces to calculate the contribution of vision to postural control. Participants are required to repeat each condition three times (Table 1). Outcome measures, including root mean square sway of the center of pressure in the anterior–posterior and medial–lateral directions (mm/s), total sway path length (mm), maximum CoP displacement in the AP and ML directions (mm), latency reaction to translation (ms), visual task accuracy (%), and the contribution of vision to balance from eye close to eye open (%), are collected at six time points, from T1 to T6.

**Table 1 Tab1:** Measurement conditions for balance test

**Conditions**		**Standing surface**	**Visual task**
**Translation**	Backward	Firm	Fixation
			Character searching
		Foam	Fixation
			Character searching
	Forward	Firm	Fixation
			Character searching
		Foam	Fixation
			Character searching
**Eye condition**	Eyes close	Firm	–
		Foam	–

Visual task (Fig. 5)

**Fig. 5 Fig5:**
[figure not shown]
Visual search task included in balance and gait test. Participants are instructed to fixate on the central dot which then changes to a “target” Chinese character “輯” for 1 s. Subsequently, an array of 8 Chinese characters, including 3 targets, are the presented for 2.5 s. After this, a mask is presented for 0.5 s. Participants are then asked to report the positions of the targets

A visual search task is included in the balance and gait tests. In this task, 8 Chinese characters arranged in a circle are presented on the screen. Some characters are targets, while others are distractors which resemble the target characters. The visual task is run using MATLAB 2020b (The MathWorks Inc, Natick, MA). Nighty eight groups of Chinese characters, each character’s number of strokes ranging from 10 to 25, are prepared for the task. All characters are presented in “Microsoft JhengHei” font on either a 14″ monitor (for balance test) or a 46″ monitor (for gait test). Each character has an angular subtense of one degree (equivalent to a visual acuity of 6/360) and is randomly presented at one of the eight positions in a circular array with an angular subtense of eight degrees. In each trial, targets and distractors are randomly positioned. Participants are asked to identify the locations of target characters among the distractors during their balance or gait test and report the locations at the end of the test. The characters, displayed in white on a black background, are placed 1 m away from the force platform in the balance test and at the endpoint of the gait path for the gait test. Before the trial, participants are asked to fixate on a black spot presented on the screen. When the experiment starts, the target character replaces the fixation spot for 1 s. This is followed by the display of an array of 8 characters for 2.5 s, a masking screen for 0.5 s (to eliminate the after-image). Participants are instructed to respond by touching the screen to indicate the locations and numbers of target characters when they are close to the monitor. The accuracy of the response is recorded and analyzed.

4)Quality of life (QoL)The ultimate objective of glaucoma rehabilitation is to sustain and enhance the QoL for patients. Therefore, it is important to evaluate whether the interventions employed in this study significantly improve QoL in glaucoma patients. The Chinese version of the National Eye Institute 25-Item Visual Function Questionnaire (NEI-VEQ-25) [51] and the Chinese version of the Low Vision Quality of Life Questionnaire (CLVQOL) [52] are used to assess vision-related QoL at four time points—T1, T4 to T6.

The NEI-VEQ-25 encompasses 12 domains: general health, general vision, ocular pain, near activities, distance activities, social functioning, mental health, role difficulties, dependency, driving, color vision, and peripheral vision [53]. Most individual items are scored by respondents using a 5- or 6-point response scale, ranging from (1) “not affected at all” to (5) “stopped doing this because of my eyesight” or (6) “stopped doing this for other reasons.” True/false items are scored on a 5-point response scale, ranging from (1) “definitely true” to (5) “definitely false,” with (3) indicating “not sure.” Responses for each item are converted to a score between 0 and 100, with higher scores representing better visual functioning [54].

The CLVQOL is a commonly used tool to examine general vision-related quality-of-life. It contains 25 closed-ended ordinal scale items including general vision and lighting, mobility, psychological adjustment, reading, fine work, and activities of daily living [52, 55]. Each item is scored on a scale of 5 (no problem due to vision) to 1 (great difficulty due to vision), with the total score being the sum of the item scores, ranging from 25 to 125. A lower total score indicates greater difficulty in performing daily life activities due to low vision.

#### Exploratory outcomes

Magnetic resonance spectroscopy (MRS)Magnetic resonance spectroscopy (MRS) is a non-invasive imaging technique that enables the measurement of the chemical composition of brain tissues. The objective of this measure is to explore the neural mechanisms that underpin visual rehabilitation by examining changes in metabolite levels. Previous research has demonstrated the role of (gamma-aminobutyric acid) GABA + in inhibitory control, while glutamate/glutamine (Glx) primarily affects excitatory control, thereby contributing to the balance between inhibition and excitation (known as the I-E balance). A recent study showed that both GABA and glutamate level was associated with glaucoma severity and targeting GABA could possibly enhance the neural specificity in visual cortex [56]. To obtain accurate metabolic concentrations, the MEGA-PRESS sequence will be used to calculate GABA + values, and the PRESS sequence will be used to measure Glx levels.

Only individuals who are physically capable will be invited to undergo the MRS scan. Participants will be required to attend two magnetic resonance imaging (MRI) sessions: one before the training intervention and another after the training (T1 and T4). Before arriving at the MRI center, the experimental procedure will be explained, and participants will complete an additional consent form for the scanning. They will also be instructed to avoid consuming caffeine and alcohol for at least 24 h prior to the scan.

The scanning procedure begins with the acquisition of a high-resolution T1-weighted image using the MPRAGE sequence, with the following parameters: TR/TE/TI: 2500/2.13/1120 ms, flip angle: 8°, bandwidth: 220 Hz, voxel size: 0.8 × 0.8 × 0.8 mm^3^, using a 64-channel head coil. An experienced radiographer will position the volume of interest (VOI) in the primary visual cortex (V1). Following this, a single-voxel MRS using the MEGA-PRESS sequence with a TE of 68 ms and TR of 1500 ms will be performed. The scan, with a voxel size of 30 × 30 × 30 mm^3^ and 160 scan averages, will be preceded by 16 averages of water reference and will take approximately 9 min. Subsequently, the PRESS sequence with a TR/TE of 3000/30 and 128 averages will be used, lasting about 5 min. This scan will also be preceded by 8 averages of water reference. Finally, a resting-state scan with a TR/TE of 2000/30 will be conducted to measure any changes in functional connectivity. To ensure consistent recordings, a photograph will be taken at each instance to document the position of V1. This will help that subsequent scans for the same participants are conducted in the exact same location.

As the MRS technique is relatively new and the analysis methods are still under development, we will employ Osprey to fit the GABA + values and GANET for the Glx values. These software tools are utilized for the precise quantification and analysis of the metabolite values derived from the MRS data. For the resting state fMRI data, a seed-based functional connectivity analysis will be employed to examine the correlation between the visual cortex and other brain regions both before and after the intervention (T1 and T4). Additionally, a network-based analysis will be used to identify any other functional changes associated with the intervention. These analysis methods will provide valuable insights into the relationships and potential alterations within the brain following the intervention.

2)Mental healthChronic diseases like glaucoma come with comorbid conditions such as depression or anxiety which can significantly decrease treatment adherence [57]. In this study, participants’ mental health is assessed using the Chinese version of the Patient Health Questionnaire-9 (PHQ-9) [58] and the Chinese version of the Perceived Stress Scale (PSS-10) [59, 60] at four time points—T1, T4 to T6. Both of them have demonstrated good validity and reliability. The PHQ-9 is a 9-item depression module, with each item scored from 0 (not at all) to 3 (nearly every day). Similarly, the PSS-10 consists of 10 items, each scored from 1 to 4. A higher total score on either scale indicates more severe depression or stress.

3)Fear of fallingFalling is a significant concern for glaucoma patients, with the fear of falling being a major contributing factor to the incidence of falls [61]. Moreover, fear of falling is associated with a decreased physical and social activity [62]. The Chinese version of the Falls Efficacy Scale-International (FES-I) is a validated and reliable questionnaire used to assess fear of falling in everyday life [63, 64]. This questionnaire includes sixteen items that are related to common daily activities, each graded on a scale of from 1 (not at all concerned) to 4 (very concerned). Higher scores indicate a greater concern about falling, which may indicate a poorer balance ability [63]. This questionnaire is conducted at four time points—T1, T4 to T6.

4)Kinetic visual fieldThe kinetic test is highly sensitive in detecting changes in the far peripheral visual field, which significantly correlates with balance function and gait performance [65, 66]. The binocular kinetic visual field is measured using Octopus 900 perimetry (Haag-Streit AG, Switzerland). Tests are done in the kinetic mode using the standard protocol (sixteen vectors), with a stimulus size of III4e moving at a speed of 5 degrees/s to map the hill of vision. Any changes in the area of the isopter over time would indicate the effect of training on the kinetic visual field [67]. Kinetic visual field is conducted at four time points—T1, T4 to T6.

5)Blood testEmerging evidence has underscored the role of neurotrophin “brain-derived neurotrophic factor” (BDNF) in controlling synaptic plasticity (e.g., improved motor skills [68] and memory [69] through BDNF secretion after anodal tDCS). Besides, a high prevalence of anxiety or depression has been observed in patients with glaucoma [70]. Cortisol, a key component of the physiological stress response, is a commonly used stress biomarker [71]. Therefore, changes in serum BDNF concentration and cortisol concentration induced by intervention will be measured before and after the training (T1 and T4). The gene that regulates BNDF varies among individuals and this genetic polymorphism can influence neural plasticity [72]. To examine the relationship between BDNF Val66Met polymorphisms (rs6265 > A) and changes in visual function following intervention, genetic analysis of BDNF Val66Met polymorphisms will be conducted before the intervention (T1).

After obtaining participants’ informed consent, a volume of 6 mL blood will be collected. Serum plasma will be analyzed using an enzyme-linked immunosorbent assay (ELISA) for blood serum BDNF and cortisol [73]. DNA will be extracted from the leucocytes for the determination of BDNF Val66Met polymorphism using a method based on polymerase chain reaction (PCR).

### Participant timeline {13}

The timeline is shown in Table 2.

**Table 2 Tab2:**
[figure not shown]
Timeline

*CLVQOL* Chinese version of the Low Vision Quality of Life Questionnaire, *EEG* electroencephalography, *FES-I* Falls Efficacy Scale-International, *HRP* high-resolution perimetry, *MRS* magnetic resonance spectroscopy, *NEI-VFQ-25* National Eye Institute Visual Function Questionnaire, *PHQ-9* Patient Health Questionnaire-9, *PL* perceptual learning, *PSS-10* Perceived Stress Scale, *QoL* quality of life, *tES* transcranial electric stimulation

^a^Eligibility test

### Sample size {14}

The sample size calculation for linear multiple regression with three groups and six time points was performed using G*Power (version 3.1). According to the HRP results from phase 1 study [37] in the GREAT project (Cohen’s *f*^2^ = 0.1), a sample of 144 glaucoma patients will be needed to provide 80% power to detect a significant difference in visual field among three groups at the 2-tailed 0.05 alpha level, assuming a 20% dropout rate.

### Recruitment {15}

Participants are being recruited from various sources including the optometry clinic at The Hong Kong Polytechnic University, Grantham Hospital, the Hong Kong Society for the Blind, self-help groups for patients, as well as private optometry and ophthalmology clinics using posters. The recruitment period started in July 2023 and is expected to end in December 2026. Recruitment is facilitated by the strategically placing posters at these locations. Moreover, to broaden our reach of this project, we have also launched advertisements on digital platforms such as YouTube and Facebook. At the stage of recruitment, participants are provided with comprehensive information about the study. This includes the timeline of the study, a detailed walkthrough of all study procedures, potential risks involved, and the benefits associated with each intervention. This ensures that participants are well informed and can make decisions based on a thorough understanding of the study.

## Assignment of interventions: allocation

### Sequence generation {16a}

A set of random numbers are generated by computer and the simple random sampling method is used to allocate the eligible participants into 3 groups.

### Concealment mechanism {16b}

An independent staff member assigns each participant a randomization number. Randomization is the only role in this project.

### Implementation {16c}

The independent staff member keeps the group assignments in a table that cannot be accessed by other members of the research team until data collection is completed and all datasets have been finalized.

## Assignment of interventions: blinding

### Who will be blinded {17a}

All eligible participants and investigators involved in the intervention and assessment procedures are blinded.

### Procedure for unblinding if needed {17b}

Unblinding will only take place after data lock. The study’s statistician, who will be unblinded, will complete the primary and secondary analyses according to the pre-specified statistical analysis plan. Other members of the study team will be granted to the unblinded datasets only after the primary and secondary analyses have been completed.

## Data collection and management

### Plans for assessment and collection of outcomes {18a}

All registered participants are recorded on a password protected glaucoma participant list and scheduled for screening eye exam using Google Calendar/Teams. All questionnaires are completed using REDCap. Raw data from measurements, including HFA, HRP, EEG, balance test, gait test, blood test, and MRI, are backed up on the hard drive. The recording forms for these measures are initially collected on paper, then scanned to create e-form after the assessments are completed. All investigators receive training in participant’s recruitment, intervention, assessments, and data backup before they participate in the project to ensure the reliability and validity of data collection process.

### Plans to promote participant retention and complete follow-up {18b}

The study aims to explore an approach that could enhance the rehabilitation of peripheral vision. The contributions of participants are highly valued and greatly appreciated throughout the study. The results of all outcomes, especially those from eye exams and balance test, are promptly shared with participants to help them fully understand their current status. In addition, a transportation allowance is provided to participants who complete all training and assessment procedures.

### Data management {19}

Deidentified data are kept in a Microsoft Teams group and on a hard drive that is accessible only to research team members. An identification number is generated for each participant to match the corresponding data files.

### Confidentiality {27}

Any information that is obtained in this study about enrolled participants will be confidential. Any publication or other public distribution of the experimental results will not include participants’ name. Raw data containing personal information will be destroyed upon the completion of this project. Research records are securely stored and only accessible for researchers. The Institutional Review Board of The Hong Kong Polytechnic University and University of Hong Kong/Hospital Authority Hong Kong West Cluster will also have access to records for the purpose of ethics review.

### Plans for collection, laboratory evaluation, and storage of biological specimens for genetic or molecular analysis in this trial/future use {33}

Blood samples are obtained from participants after obtaining informed consent. The venipuncture method is used, employing a sterile needle and syringe in conjunction with the vacutainer blood collection system. A volume of 6 mL of blood is collected from the antecubital vein into Greiner Bio-One 6 mL Vacuette Tubes. The collected blood is then allowed to clot undisturbed at ambient temperature for a duration of 30 to 60 min. To separate the serum from other blood constituents, the clotted blood is centrifuged at a force of 3000 × g and a temperature of 4 °C for 20 min. The resulting serum is transferred to a labeled 1 mL Eppendorf tube. To preserve the integrity of the serum samples, they are stored at a temperature of − 30 °C for further analysis.

## Statistical methods

### Statistical methods for primary and secondary outcomes {20a}

At the conclusion of this project, we will perform statistical analysis based on the intention-to-treat (ITT) principle. For the primary outcome, the differences of MD measured using the 24–2 SITA HFA will serve as an indicator of the effectiveness of interventions. Among the three groups, the intervention group showing the greatest improvement in MD will signify the strongest impact of rehabilitation. Additionally, changes in MD across six time points (baseline, interim 1, interim 2, post-intervention, 1-month post-intervention, and 2-month post-intervention) will reveal the dose-response relationship and recovery duration.

To address inter-individual variability, we will employ a linear mixed model with intervention type and time point as the fixed effect, and baseline MD value as the covariate. A dummy-coding scheme with the placebo PL + sham tES condition as the reference level will be utilized. Initially, a full model will be fitted, and if convergence issues or overfitting arise, adjustments will be made to the random intercept and slope. Model comparison will be conducted using a likelihood-ratio test to evaluate the adequacy of the current model relative to alternative models without the fixed effect. The level of statistical significance for analysis is set at a two-sided *p* < 0.05.

To address the potential attrition and missing data due to participant drop-out, we will conduct sensitivity analyses using multiple imputation methods. Specifically, we will employ the fully conditional specification (FCS) method. This method allows for the imputation of missing data for multiple variables with different distributions. By conducting these sensitivity analyses, we aim to assess the robustness of our primary analysis results to potential attrition bias and missing data. The multiple imputation approach will provide a principled way to handle missing data, ensuring that our conclusions are not unduly influenced by the potential non-random nature of missing data.

The analyses of secondary and exploratory outcomes will follow a similar approach to that of the primary outcome. A detailed statistical analysis plan for secondary and exploratory outcomes is being developed and will be reviewed of by the steering group prior to data analysis.

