#### Primary outcome

Visual field test is measured monocularly using the 24–2 and 10–2 Swedish interactive threshold algorithm (SITA) standard tests by Humphrey visual field analyzer (HFA, Carl Zeiss Meditec Inc., California). The mean deviation (MD), pattern standard deviation (PSD), and visual field index (VFI) are recorded and the MD of 24–2 visual field test is used as primary outcome of intervention effectiveness. HFA visual field test is conducted at six time points, from T1 to T6.

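### The primary outcome (24-2 MD) has no deciding visit, summary over visits or eye, and its two placebo-referenced contrasts share one unadjusted 5% level

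*Protocol article*

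**What the plan says.** - **Outcome.** Under Primary outcome, "the MD of 24–2 visual field test is used as primary outcome of intervention effectiveness", and "HFA visual field test is conducted at six time points, from T1 to T6". T1 is baseline. T2, T3 and T4 follow 10, 20 and 30 sessions, and T5 and T6 come one and two months after training. The test is monocular. Under Intervention description {11a}, one eye, the one with the lesser field defect, is the training eye. The outcome is not tied to it.
- **Effect.** Under Statistical methods {20a}, "the differences of MD measured using the 24–2 SITA HFA will serve as an indicator of the effectiveness of interventions". The arm with the largest MD improvement is taken to have the strongest effect, with no visit given. The time course is introduced as an addition that "will reveal the dose-response relationship and recovery duration".
- **Model.** A "linear mixed model with intervention type and time point as the fixed effect, and baseline MD value as the covariate". No group-by-time term is named.
- **Contrasts and level.** "A dummy-coding scheme with the placebo PL + sham tES condition as the reference level will be utilized". "The level of statistical significance for analysis is set at a two-sided" p < 0.05, with no order or adjustment stated.
- **Overall test.** A likelihood-ratio test is used "to evaluate the adequacy of the current model relative to alternative models without the fixed effect". It is not described as a condition for reading the contrasts.
- **Timing and plan.** Interim analyses {21b} puts all analysis at the end. Unblinding {17b} has an unblinded statistician run the primary and secondary analyses under a pre-specified plan. Section {20a} announces a detailed plan for secondary and exploratory outcomes only.

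**The concern.** A variable becomes a primary endpoint only when the time point (or summary over time) and the unit measured are fixed. Here the variable is fixed and the rest is open. The visits answer different questions: T2 reflects a third of the training, T4 the full course, and T6 durability. The arms could rank differently at each, so the rule that the arm with the greatest improvement shows the strongest effect has no single answer. The trained and untrained eyes could also disagree.

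Separately, two contrasts against a shared control are each read at the full 5%. The chance of at least one false claim therefore exceeds 5% even if the time point were settled.

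At stake is whether the superiority claim carries its stated error rate. As the text stands, the choice of visit and eye could be made by an unblinded statistician with all visits in hand.

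**Working it through.** **Inputs from the protocol:** three arms at 1:1:1; two contrasts against placebo PL + sham tES; five post-baseline visits; two-sided 0.05.

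**Assumption:** the correlation r between visits is not given, so a range is shown. It is taken as equal for every pair of visits.

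**The plan's own figure.** The sample size of 144 reproduces. A multiple-regression F test with f² = 0.1, 80% power and three predictors (the count is assumed) needs 114. Then 114 / 0.8 = 142.5, so 143, or 144 as 48 per arm. This point does not affect that figure.

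**Step 1: the model read literally.** With main effects only, each contrast is one average effect over visits. With equal arms and a shared control, the two z statistics have correlation 0.5. Independent tests would give 1 − 0.95² = 9.75%. With the shared control, simulation under no effect (300,000 trials per setting) gives P(|Z₁| > 1.96 or |Z₂| > 1.96) ≈ 9.1%, and 9.1 / 5 = 1.8 times the stated level. Naming a single visit leaves the same 9.1%. Adding the contrast of combined therapy against PL alone, which the first hypothesis calls for, makes it 12.2% at one visit.

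**Step 2: if arm differences were tested visit by visit and any visit could count.** For independent visits, one contrast gives 1 − 0.95⁵ = 22.6%. Simulated chance of at least one p < 0.05 over T2–T6:

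| r (assumed) | One contrast | Two contrasts |
|---|---|---|
| 0 | 22.6% | 37.9% |
| 0.5 | 18.2% | 31.0% |
| 0.8 | 12.9% | 22.4% |
| 0.9 | 10.1% | 17.8% |
| 0.95 | 8.5% | 15.1% |

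For r from 0.9 to 0.5, the visits alone multiply the 5% by 10.1 / 5 = 2.0 to 18.2 / 5 = 3.6, and by no more than 22.6 / 5 = 4.5 at r = 0. Visits and both contrasts together multiply it by 17.8 / 5 = 3.6 to 31.0 / 5 = 6.2.

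**Step 3: with a gate at one named time point.** If no arm differs, a false claim first requires the 2-df test to be significant, so the rate is at most 5% (simulated 4.9–5.0%). If exactly two arms are equal, only one pairwise null hypothesis is true, and it is tested at 5%. With three arms the gate therefore controls family-wise error without splitting alpha.

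**The case against.** 1. **Any-visit success is not in the text.** A reader might infer that a significant difference at any visit would count, so that the false-positive rate is 2 to 6 times 5%. The documents do not support this. No such rule is written, and the model names no group-by-time term. The time course has a stated descriptive role. The sample-size section speaks of a difference among three groups, which suggests one overall comparison. The multiple also depends on assumed correlations, and its upper end comes from combining visits with contrasts. This objection stands, so the visit-by-visit figures are conditional.

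2. **A plan may settle it.** Unblinding {17b} refers to a pre-specified plan that covers the primary analysis, and the article condenses a fuller protocol. It would be wrong to infer from {20a} alone that the primary rule is final. This stands in part: order of testing and alpha allocation are often left to such a plan. But the deciding time point and eye belong to the endpoint's definition. The article states that endpoint in the abstract, the outcome section and the statistical section, each time without them.

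3. **The likelihood-ratio test could serve as the group test.** On that reading the rate would be 5%. The text gives it another purpose, however, and does not say whether group, time or both are dropped from the comparison model.

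4. **The average effect is a legitimate endpoint.** It is, if stated. It is stated nowhere, and the second hypothesis (effect growing with training) and the recovery aim need arm differences by visit.

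**Conclusion.** The point holds in a limited form. The protocol fixes the primary variable but not the visit, summary over visits or eye. It reads two contrasts at an unadjusted 0.05 without a gate. On the literal model, family-wise error is about 9% rather than 5%, which needs no assumption about between-visit correlation. The larger figures, about 10–18% for one contrast and 18–31% for two, apply only if visits were tested separately and any could count. They also assume correlations of 0.9 to 0.5. The protocol leaves that possibility open but does not state it, so a fixed inflation of 2 to 6 times should not be attributed to it. The gap is still more than missing detail, because the visit and eye could be settled after unblinding with every visit available.

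**What to change.** Before data lock, state under Primary outcome and in {20a}, or in the pre-specified plan that {17b} mentions:

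1. The primary endpoint is 24-2 MD of the training eye at one named time point. T4, at the end of the 30 sessions, is one defensible choice. A stated average over visits is another.
2. The effect is the baseline-adjusted arm difference at that time point, estimated from the mixed model with a group-by-time term.
3. The 2-df group difference at that time point is tested first at two-sided 0.05. Pairwise contrasts follow, each at 0.05, only if it is significant.
4. The remaining visits (dose-response, durability) and the fellow eye are supportive, reported with confidence intervals and without a confirmatory claim.

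The cost is wording, with no new patients or data. The small downside is that a difference seen only at another visit can no longer be claimed as primary success. The sample-size text refers to six time points, and the protocol does not give enough to work out power at a single visit, so the team should check power for the time point it chooses.
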